### Data collection and management

2.12

Data will be recorded in Case Report Forms (CRFs) and include preoperative details like demographics, pulmonary function (FEV1/FVC), surgical type (segmentectomy, lobectomy, wedge resection, other), surgery duration, and intubation type (double-lumen tube or bronchial blocker). Postoperative data will include pulmonary function, NRS scores, QoR-15, delirium, incidence of postoperative nausea and vomiting, and gastrointestinal recovery. Data were collected and managed using REDCap, a secure electronic data capture system compliant with ICH-GCP and applicable regulatory requirements. CRFs were designed according to the study protocol and CDASH standards. Real-time data validation, including range checks and logical consistency, was programmed into the system. Discrepancies and queries were resolved by investigators through the EDC platform, with all modifications tracked by an audit trail. External laboratory data were imported electronically to reduce manual entry errors. Following completion of data collection, the database underwent a final review, was locked, and then exported for statistical analysis.

### Sample size calculation

2.13

Our preliminary findings indicate a 70% incidence of moderate-to-severe pain postoperatively. Given prior studies reporting analgesic effects of rTMS over the M1 region, we hypothesize that a reduction in moderate-to-severe pain incidence to 50% following two interventions would constitute an effective therapeutic response (37). With α = 0.05 and β = 0.2 (80% power), the required sample size is 103 per group. Considering a 10% dropout rate and future subgroup analyses, we aim to recruit 260 patients, randomly assigned to active and sham stimulation groups.

### Statistical analysis

2.14

Analysis will follow the intention-to-treat (ITT) principle using SPSS 27.0, with graphs created in GraphPad Prism 8.0. The Kolmogorov-Smirnov test will check normality, and Levene’s test will evaluate variance homogeneity. Data will be presented as mean ± standard deviation for normal distributions and median with interquartile range for non-normal distributions.

Continuous variables will be assessed with the *t*-test or Mann-Whitney U test, depending on distribution. Categorical variables, including the primary outcome, will be examined using chi-square tests or Fisher’s exact test, with differences shown as relative risk and 95% CI. Comparisons of primary outcomes used generalized estimating equations (GEE). The interaction between treatment and time was first assessed. If this interaction was statistically significant, Bonferroni-corrected multiple comparisons were performed to assess differences between groups at each individual time point. If not, the primary treatment effect was then assessed at each time point without applying the Bonferroni correction. For other replicated measurement data, GEE were similarly employed for analysis. Multivariate analysis will use linear or logistic regression models based on the outcome type. Missing data will be addressed with multiple imputation, and a per-protocol analysis will be included for sensitivity. Benjamini-Hochberg correction for secondary outcomes. A significance level of α = 0.05 will be applied, with *p* < 0.05 deemed significant.

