
**TABLE 1 T1:** The study schedule for enrollment, treatments, outcome measurements, and data collection.

Study period									
Time point	Enrollment		Post-randomization						
	Pre-2	Pre-1	30 min before surgery	2 h after surgery (T1)	6 h after surgery (T2)	12 h after surgery (T3)	24 h after surgery (T4)	48 h after surgery (T5)	90 days after surgery (T6)
Enrollment									
Inclusion criteria	✓	–	–	–	–	–	–	–	–
Exclusion criteria	✓	–	–	–	–	–	–	–	–
Informed consent	✓	–	–	–	–	–	–	–	–
Randomization	–	✓	–	–	–	–	–	–	–
Interventions									
Active rTMS group	–	✓	✓	–	–	–	–	–	–
Sham rTMS group	–	✓	✓	–	–	–	–	–	–
Outcome measurement									
Postoperative resting pain score (NRS)	–	–	–	✓	✓	✓	✓	✓	✓
Postoperative movement pain scores (NRS)	–	–	–	✓	✓	✓	✓	✓	✓
Postoperative recovery quality index (QoR-15)	–	–	–	–	–	–	✓	✓	–
Remedial analgesic dosage (MME) in the first 48 h postoperatively	–	–	–	–	–	–	–	✓	–
Incidence of moderate to severe pain at 24 h postoperatively	–	–	–	–	–	–	✓	–	–
Adverse events	–	–	–	✓	✓	✓	✓	✓	✓

According to SPIRIT 2013 statement: defining standard protocol items for clinical trials. Pre-2, 2 days prior to the surgery; pre-1, the day before the surgery; MME, morphine mg equivalent; QoR-15, Quality of Recovery-15.

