#### Primary outcome

2.10.1

The primary outcome is the incidence of moderate-to-severe pain at 24 h postoperatively. APSP is common after VATS, often peaking within 24–48 h (32). Pain can inhibit breathing leading to atelectasis and impair postoperative mobility and physiotherapy (33). Pain intensity will be recorded using the Numerical Rating Scale (NRS) (34). An NRS score ≥ 4 is defined as moderate-to-severe pain (35). The primary outcome measure will be the NRS score for the most severe pain experienced within 24 h, recorded prior to any rescue analgesic administration.

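### Section 2.14 assigns the single 24 h primary outcome to two incompatible analyses, chi-square/Fisher and an interaction-gated GEE, and does not say which governs

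*Protocol article*

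**What the plan says.** The endpoint is defined in the Primary outcome section (2.10.1): "The primary outcome is the incidence of moderate-to-severe pain at 24 h postoperatively". The cut-off is given there as "An NRS score ≥ 4 is defined as moderate-to-severe pain", and the underlying measurement as "The primary outcome measure will be the NRS score for the most severe pain experienced within 24 h". Table 1 has a row for "Incidence of moderate to severe pain at 24 h postoperatively", ticked at T4 (24 h) only.

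The sample size section (2.13) assumes 70% in the control group and 50% in the active group: "With α = 0.05 and β = 0.2 (80% power), the required sample size is 103 per group". It then allows for 10% dropout and future subgroup analyses and aims for 260 patients, randomised 1:1.

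The Statistical analysis section (2.14) contains two instructions for the primary outcome, in consecutive sentences:

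- The first is "Categorical variables, including the primary outcome, will be examined using chi-square tests". Its stated alternative is Fisher's exact test, and the effect measure is a relative risk with its 95% CI.
- The second, immediately after it, is "Comparisons of primary outcomes used generalized estimating equations (GEE".

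The second instruction continues with a gate. The treatment-by-time interaction is tested first. If it is significant, the between-group comparisons at each time point are Bonferroni-corrected; if not, each time point is tested without correction. The section then extends GEE to the other repeated data.

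**The concern.** The two instructions are alternatives, and the plan gives no order of precedence. They differ in the data they need, in the hypothesis they test and in the alpha at which 24 h is judged.

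The second also does not fit the endpoint. A treatment-by-time interaction needs at least two time points per patient, and the primary outcome has one. To run GEE at all, the analyst must substitute another variable, such as NRS ≥ 4 at each scheduled assessment. The 24 h result would then be judged at 0.05 or at a fraction of it, depending on what happens at other times, possibly including day 90.

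At stake is which p-value decides the trial. If the two routes disagree, the protocol as written supports either. In one branch of the GEE route, the trial would also be tested at an alpha for which it was not sized.

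**Working it through.** **1. Does the endpoint have a time dimension?** Section 2.10.1 gives one NRS-based classification per patient, and Table 1 ticks it once, at T4. Section 2.10.2 lists T1–T6 for resting and movement NRS scores, which are secondary outcomes. No repeated NRS ≥ 4 outcome is defined anywhere. The interaction gate therefore cannot be computed on the stated primary outcome.

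**2. Which analysis was the trial sized for?** Inputs from section 2.13: p1 = 0.70, p2 = 0.50, d = 0.20, α = 0.05, power 80%. Two-sided testing is assumed, because sidedness is not stated. Mean proportion 0.60.

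- √(2 × 0.60 × 0.40) = 0.6928; √(0.70 × 0.30 + 0.50 × 0.50) = 0.6782.
- Uncorrected n = (1.960 × 0.6928 + 0.8416 × 0.6782)² / 0.20² = 1.9287² / 0.04 = 93.0.
- Continuity-corrected n = (93.0 / 4) × [1 + √(1 + 4 / (93.0 × 0.20))]² = 23.25 × 2.1023² = 102.8, rounded up to 103.

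This matches the protocol exactly. The other variants tried do not: uncorrected pooled 93, unpooled 91, one-sided 74 (83 with correction). So 103 is the size for one two-proportion test at two-sided 0.05, with no time factor and no split of alpha. Dropout gives 103 / 0.9 = 114.4, so 115 per group or 230 in total. Recruiting 260 gives 130 per group, or 130 × 0.9 = 117 evaluable.

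**3. Power for the 24 h contrast if the Bonferroni branch applied.** The number of time points K is an assumption: 6 (T1–T6) or 5 (T1–T5).

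Power = Φ{[√n × (d − c) − z × 0.6928] / 0.6782}, with c = 0 (uncorrected) or c = 1/n (continuity-corrected), and z taken at two-sided α = 0.05/K: 1.960 for a single test, 2.576 for K = 5, 2.638 for K = 6.

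Example, n = 103, K = 6, uncorrected: (10.149 × 0.20 − 2.638 × 0.6928) / 0.6782 = 0.298, and Φ(0.298) = 61.7%.

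| Evaluable per group | Single test at 0.05 | K = 5 (α = 0.01) | K = 6 (α = 0.00833) |
|---|---|---|---|
| 103, uncorrected / corrected | 83.9% / 80.1% | 64.1% / 58.6% | 61.7% / 56.1% |
| 117, uncorrected / corrected | 88.3% / 85.3% | 71.2% / 66.4% | 69.0% / 64.0% |
| 130, uncorrected / corrected | 91.3% / 89.1% | 76.8% / 72.6% | 74.8% / 70.5% |

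The corrected figures are on the basis that reproduces 103. Exact enumeration of the chi-square test gives 62–64%, 70–71% and 75–77% for K = 6 and 5, in line with the uncorrected column. Keeping 80% in this branch would need 139 (K = 5) or 144 (K = 6) evaluable per group uncorrected, or 149 and 154 corrected. All exceed the 130 per group to be randomised.

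**4. Power over both branches.** The gated procedure was simulated with six correlated binary time points and 3,000 runs per setting. A Wald test of equal risk differences over time stood in for the interaction test. Control rates were assumed at 60, 60, 65, 70, 60 and 30% for T1–T6, with latent correlation 0.3–0.7 and three assumed effect profiles, each with 70% against 50% at 24 h. Power for the 24 h contrast was 67–76% at 103, 73–82% at 117 and 78–86% at 130 per group, against about 83–92% for the ungated test. Under the null, the 24 h contrast was declared significant in 4.1–4.9% of runs.

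**The case against.** The strongest reply is that the document leans clearly to one analysis. The chi-square sentence names the primary outcome in the singular and gives its effect measure, and the sample size matches that test to the patient. The GEE sentence may simply be misplaced text meant for the repeated NRS scores. This is plausible, but the text does not settle it. The later sentence extends GEE to the *other* repeated data, which implies that the primary outcome is itself being treated as repeated data.

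A second reply is that the power argument sits awkwardly with the first: if no interaction exists for the endpoint, no Bonferroni branch exists either. That stands as a limit. The power figures describe what would follow if someone made the GEE route runnable by substituting a repeated binary outcome. They do not describe the protocol's stated endpoint.

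Three stronger readings are tempting, and the protocol does not support them:

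- A reader might infer that the trial is underpowered. It is not under the chi-square route, and under the GEE route the loss needs a significant interaction. Over both branches, the simulated power at 117 and 130 per group falls on either side of 80%, depending on assumed profiles.
- A reader might infer that the gate inflates the false-positive rate at 24 h. In the simulation it did not.
- A reader might take the sentence on linear or logistic regression as a third primary analysis. It is a generic sentence keyed to outcome type and does not claim that role.

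**Conclusion.** The point holds. Section 2.14 prescribes two incompatible analyses of the primary outcome, and one of them cannot be run on the outcome as defined. This follows from the text alone and needs no assumption. It is a contradiction rather than an omission, so a separate analysis plan would not make this section correct as it stands.

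The consequence for power is conditional. It requires that GEE be applied to NRS ≥ 4 at five or six time points, that the interaction be significant, and that the rates be 70% and 50%. Power for the 24 h contrast is then about 56–64% at 103, 64–71% at 117 and 70–77% at 130 evaluable per group, over both values of K and with or without continuity correction. If the interaction is not significant, the 24 h comparison stays at 0.05 and keeps its planned power. The sample size of 103 is not itself wrong; it belongs to the chi-square route.

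This must be fixed. The study design section says that recruitment is under way, so the choice should be recorded before anyone sees outcome data by group.

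**What to change.** In section 2.14:

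- State that the sole primary analysis is the chi-square (or Fisher's exact) comparison of the 24 h proportion with moderate-to-severe pain, at two-sided α = 0.05, reported as relative risk and risk difference with 95% CIs. This matches section 2.13.
- Delete the sentence applying GEE to the primary outcomes, and remove the interaction gate from the primary analysis.
- Confine GEE to the repeated resting and movement NRS scores, as secondary outcomes.

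The cost is a few sentences in a dated amendment. Sample size, data collection and patient procedures do not change. The same amendment could settle whether the primary value is pain at 24 h or the worst pain within 24 h, since section 2.10.1 uses both. Either way it remains one value per patient, so the fix above does not depend on that answer.

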### Randomization and blinding

2.6

Using a random block allocation method (block sizes of 4 and 6), subjects were assigned in a 1:1 ratio to either the active or sham rTMS group. The sequence for randomization will be produced by an individual statistician who is not involved in the recruitment of patients or the assessment of outcomes, using SAS software (version 9.4; SAS Institute, Cary, North Carolina, United States). This serial number will be enclosed in a sequentially numbered, impervious to light, sealed envelope. Upon eligibility confirmation and consent, the researcher will open the next envelope in sequence and execute the assignment. Sequentially numbered, opaque, sealed envelopes will be opened only after participant enrollment and consent. The envelope will not be resealed. To assure compliance with the Blind Method, patients will be informed during preoperative consultations about potential sensations experienced during therapy, including tapping, pricking, warmth, or vibration. Patients will also be explicitly advised that the intensity of these sensations varies among individuals and should not be used as a basis for evaluating treatment efficacy. The stimulation devices are identical in appearance; the only difference lies in the placement angle of the coil during stimulation. The device is to be managed by independent researchers not participating in the study, and the screen is to remain off prior to treatment. Each participant will complete a questionnaire after the intervention to infer group assignment, with data reported and analyzed using the Bang blind index. All personnel involved in outcome assessment, data analysis, surgery, and the participants themselves will be blinded to group assignment. The outcome evaluators will undergo rigorous blinding training prior to the study commencement to familiarize themselves with operational processes and standards, thereby minimizing the impact of subjectivity on results.

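### When treatment-by-time is not significant, the plan tests every time point without Bonferroni instead of one overall effect; for the six-point pain scores this gives about a 15–22% false-positive chance per outcome unless Benjamini-Hochberg spans time points

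*Protocol article*

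**What the plan says.** Section 2.14 of the protocol article assigns GEE to the primary outcome and starts with the treatment-by-time interaction. If the interaction is significant, the groups are compared at each time point with Bonferroni. Otherwise: "If not, the primary treatment effect was then assessed at each time point without applying the Bonferroni correction".

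The approach is then extended: "For other replicated measurement data, GEE were similarly employed for analysis". Under Secondary outcomes (2.10.2) and Table 1, the repeated measures are resting NRS and movement NRS, each at six times (2, 6, 12, 24 and 48 h, and 90 days), and QoR-15 at two times (24 and 48 h).

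Two further sentences bear on error control: "Benjamini-Hochberg correction for secondary outcomes", with no statement of which p-values form the family, and "A significance level of α = 0.05 will be applied".

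Primary outcome (2.10.1) and Table 1 place the primary outcome at 24 h only. Section 2.14 also assigns it a chi-square or Fisher's exact test with a relative risk.

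**The concern.** A gate on the interaction has one purpose. If the effect appears to change over time, look at the times separately; if not, summarise it once. The first branch here is conventional. The second does not summarise: it still looks at each time separately, and with less protection than the first. A non-significant interaction does not reduce the number of tests and gives no reason to drop their adjustment.

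At stake are the two pain-score outcomes, the most visible repeated measures in the trial. With no effect at any time, an analyst following the text would fairly often find some significant time point to report. A real, steady effect would be spread over several separate tests in place of one GEE estimate.

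The clause also sits directly after the sentence giving GEE to the primary outcome. An outcome defined at one time has no treatment-by-time interaction, so a reader cannot tell whether other time points may be presented as primary results.

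**Working it through.** **Inputs from the documents.** Nominal level 0.05 (2.14); six time points for each NRS outcome, or five if day 90 is left out; two for QoR-15 (2.10.2, Table 1). Sidedness is not stated.

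**Check on sidedness.** The sample size section starts from "Our preliminary findings indicate a 70% incidence of moderate-to-severe pain postoperatively" and "a reduction in moderate-to-severe pain incidence to 50% following two interventions", and concludes: "With α = 0.05 and β = 0.2 (80% power), the required sample size is 103 per group". With a two-sided 0.05 test and 1:1 allocation:

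- n = [1.96·√(2·0.6·0.4) + 0.8416·√(0.7·0.3 + 0.5·0.5)]² / 0.2² = (1.3579 + 0.5708)² / 0.04 ≈ 93 per group.
- With continuity correction: (93/4)·[1 + √(1 + 4/(93·0.2))]² = 23.25 × 4.420 ≈ 103.

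This reproduces the stated 103, so two-sided 0.05 is used below.

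**Assumption.** The documents give no within-patient correlation between time points. It is varied over 0.3, 0.5 and 0.7 (exchangeable), with wider values as a check.

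**Upper reference, no gate and independent tests.** 1 − 0.95⁶ = 26.5%; 1 − 0.95⁵ = 22.6%; 1 − 0.95² = 9.75%.

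**The plan as written, no effect at any time.** Simulation of correlated standard normal test statistics, at least 400,000 draws per scenario. The interaction is a Wald test on k − 1 degrees of freedom at 0.05. If it is significant, each time point is tested at 0.05/k; if not, at 0.05. The entries are the probability of at least one significant time point.

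| Time points | corr. 0.3 | corr. 0.5 | corr. 0.7 |
|---|---|---|---|
| 6 (NRS, T1–T6) | 21.5% | 18.6% | 15.0% |
| 5 (NRS, T1–T5) | 18.5% | 16.4% | 13.5% |
| 2 (QoR-15) | 8.6% | 8.4% | 7.8% |

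For six points at correlation 0.5, the split is 0.95 × 18.5% (uncorrected branch) + 0.05 × about 20% (Bonferroni branch) = 17.6% + 1.0% = 18.6%. Almost all of the error comes from the faulty branch.

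**Wider range, six points.** 24.0% at correlation 0 and 12.8% at 0.8. With first-order autoregressive correlation of 0.5, 0.7 and 0.8: 21.0%, 17.8% and 15.6%.

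**If Benjamini-Hochberg did span the time points of an outcome.** Using it in the non-significant branch gives 4.8%, 4.4% and 3.8% for six points at correlations 0.3, 0.5 and 0.7.

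**The 24 h comparison alone.** Put through the same six-point gate, it rejects 4.4%, 4.5% and 4.6% of the time.

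**After correction, six points.**

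- One averaged effect at 0.05 in the non-significant branch, Bonferroni kept in the other: about 6.3%, 5.8% and 5.4% (5.3% on a repeat run at correlation 0.7).
- The averaged effect tested whatever the interaction shows: 5.0%.
- Bonferroni on time points in both branches: 4.7%, 4.1% and 3.3%.

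**The case against.** Four points can fairly be made for the plan.

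*The primary conclusion is safe.* A reader might infer from the clause that the main result of the trial carries an error of 15% or more. The documents do not support that. The primary outcome is one comparison at 24 h, and that comparison stays below 5% even inside the gate. The larger figure needs significance at any of several times to count as success, which section 2.10.1 does not allow. What stands is narrower: section 2.14 names both a gated GEE and a chi-square or Fisher test for an outcome measured once.

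*Benjamini-Hochberg may already cover it.* Dropping Bonferroni is not the same as dropping every correction. If the false-discovery correction runs across time points, the pain-score error is under 5%. This stands as a condition on the finding. The text does not define the family, however, so the protection cannot be assumed. It is also too strong to say that the same p-value is declared uncorrected, Bonferroni-corrected and FDR-corrected: the first two belong to alternative branches and never meet.

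*The gate is not reversed.* That is another tempting description, but the significant-interaction branch is standard. One clause is faulty. It may be a slip for the *main* treatment effect, but a main effect is not assessed time point by time point, so the sentence needs correction on either reading.

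*Single summaries already exist.* The AUCs for resting and movement pain over T1–T5 are prespecified, so a steady effect is not lost altogether. That limits the loss of efficiency but does not repair the time-point tests.

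**Conclusion.** The non-significant branch is a stated rule that gives a wrong result and should be corrected. For each NRS outcome, the chance of at least one false-positive time point is about 15–22% with six time points (13.5–18.5% with five), and about 8–9% for QoR-15, against a nominal 5%.

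These figures assume no effect at any time, large-sample normal statistics, a correlation of 0.3–0.7 that the documents do not supply, and a Benjamini-Hochberg correction that does not span time points. The excess for the pain scores remains at every correlation tried from 0 to 0.8. It disappears only if the last assumption fails.

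The error rate of the 24 h primary comparison is not affected. For that outcome the defect is one of wording: the gate should not be attached to it, and a significant result at another time must not count as a primary result.

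**What to change.** Reword section 2.14 as follows.

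1. Replace the faulty clause: for each repeated secondary outcome, when the interaction is not significant, test one time-averaged treatment effect from the GEE (whole-procedure error about 5.3–6.3%). Reporting that effect whatever the interaction result is cleaner and gives 5.0%. State which time points the average covers; whether day 90 belongs in it is a design choice to be declared.
2. Give time-specific differences with 95% confidence intervals as descriptive results, or adjust them for multiplicity in both branches.
3. State that the Benjamini-Hochberg family takes one p-value per secondary outcome.
4. Confine the primary test to the 24 h comparison, outside the gate, with one named method.

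The cost is a few reworded sentences and fewer time-point p-values to report. Sample size, visits and data collection do not change. Recruitment is under way and an interim analysis is planned at about half of the data, so the change should be dated before any unblinded look.

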#### Secondary outcomes

2.10.2

The postoperative period is defined as starting from the time of PACU admission.

(1).Time to first PCIA demand (from surgery end to first effective PCA button press with drug delivery).(2).Resting pain scores (NRS) at 2 h (T1), 6 h (T2), 12 h (T3), 24 h (T4), 48 h (T5), and 90 days (T6) postoperatively. Resting pain is assessed while the patient is lying quietly.(3).Movement pain scores (NRS) at T1–T6 postoperatively. Movement pain is assessed during turning or coughing.(4).PACU length of stay (hours from PACU admission to discharge).(5).Area under the curve (AUC) for resting pain scores from T1 to T5 (0–48 h), calculated using the trapezoidal rule, to quantify total pain burden.(6).AUC for movement pain scores from T1 to T5 (0–48 h), calculated using the trapezoidal rule.(7).Quality of Recovery assessed by QoR-15 score at 24 h (T4) and 48 h (T5) postoperatively.(8).Extubation time (minutes from cessation of all maintenance anesthetics to safe removal of the endotracheal tube). The decision to extubate, made by a blinded anesthesiologist, will be based on standard clinical criteria.(9).Record the dosage of rescue analgesics administered within 48 h postoperatively, expressed in milligram equivalents of oral morphine (MME). Rescue analgesia is administered according to the protocol if the patient’s resting pain numerical rating scale (NRS) score is ≥4 within 48 h postoperatively. For standardized comparison, all opioid medications are converted to milligram equivalents of oral morphine based on the American Academy of Pain Medicine guidelines (36).

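### When the treatment-by-time interaction is not significant, section 2.14 tests each time point uncorrected instead of making one overall treatment test; this affects the repeated secondary outcomes, not the 24 h primary comparison

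*Protocol article*

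**What the plan says.** Section 2.14 (Statistical analysis) introduces a two-branch rule with "Comparisons of primary outcomes used generalized estimating equations (GEE". The treatment-by-time interaction is tested first. If it is significant, the groups are compared at each time point with Bonferroni correction. The other branch reads: "If not, the primary treatment effect was then assessed at each time point without applying the Bonferroni correction". The rule is then carried over to the rest of the repeated data: "For other replicated measurement data, GEE were similarly employed for analysis". The section describes no single overall treatment test from the GEE.

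The same section also assigns the primary outcome to a chi-square or Fisher's exact test, applies a Benjamini-Hochberg correction to secondary outcomes without saying what its family contains, and sets the level: "A significance level of α = 0.05 will be applied, with *p* < 0.05 deemed significant".

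Section 2.10.1 and Table 1 place the primary outcome, a yes/no incidence, at 24 h only. Section 2.10.2 lists the repeated series as secondary: resting NRS at T1–T6, "Movement pain scores (NRS) at T1–T6 postoperatively", and QoR-15 at 24 and 48 h. It also lists an AUC over T1–T5 for each pain series.

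**The concern.** The second branch runs the wrong way. If the interaction is not significant, the data give no evidence that the effect changes over time, and the matching analysis is one treatment effect with one p-value. The plan instead opens up to six tests per pain series and removes the correction at that point. When treatment does nothing, the interaction test is non-significant about 95% of the time, so the uncorrected branch is the one nearly always used when a false positive can arise.

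At stake are the claims on the secondary pain and recovery series: one isolated time point below 0.05 could be reported as evidence of analgesia. This is a rule that the text states, not a detail left to a later document.

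**Working it through.** **The plan's own figure.** Inputs from section 2.13: "Our preliminary findings indicate a 70% incidence of moderate-to-severe pain postoperatively", "a reduction in moderate-to-severe pain incidence to 50% following two interventions", and "With α = 0.05 and β = 0.2 (80% power), the required sample size is 103 per group".

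- Without continuity correction: n = [1.96·√(2·0.6·0.4) + 0.8416·√(0.7·0.3 + 0.5·0.5)]² / 0.2² = (1.358 + 0.571)² / 0.04 ≈ 93.
- With continuity correction: n = (93/4)·[1 + √(1 + 4/(93·0.2))]² = 23.25·(2.102)² ≈ 102.8, so 103.

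The 103 is reproduced. It is sized for one two-sided comparison of two proportions at 0.05, which fits a single 24 h primary test. The plan states no family-wise error rate for the GEE rule, so there is no stated figure to reproduce for that.

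**Upper bound for uncorrected tests.** For K independent tests the chance of at least one false positive is 1 − 0.95^K: 9.75% (K = 2), 22.6% (K = 5), 26.5% (K = 6).

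**The whole rule.** I simulated it under no treatment effect at any time point: 500,000 replicates, two-sided z tests (sidedness is not stated, so this is assumed), and a Wald interaction test on K − 1 contrasts at 0.05. If that test is significant, each point is tested at 0.05/K; if not, each at 0.05. The correlation between time points is not in the documents, so it is varied (exchangeable). The last column applies Benjamini-Hochberg across the six time points instead of the rule.

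| Correlation | Rule, 5 points | Rule, 6 points | Benjamini-Hochberg, 6 points |
|---|---|---|---|
| 0 | 20.2% | 23.9% | 5.0% |
| 0.3 | 18.4% | 21.4% | 4.8% |
| 0.5 | 16.3% | 18.6% | 4.4% |
| 0.7 | 13.5% | 15.0% | 3.8% |
| 0.9 | 9.4% | 10.0% | 3.1% |

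With an autoregressive correlation of 0.5, 0.7 or 0.9, six points give 21.0%, 17.9% and 12.2%. Two time points (QoR-15) give about 7–9%.

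**Where the error comes from.** Six points, correlation 0.5: given a non-significant interaction, the error is 18.5%. That branch contributes 0.95 × 18.5% ≈ 17.6 of the 18.6 percentage points; the Bonferroni branch adds only about 1.0.

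**The single 24 h comparison.** Tested alone, it stays at 5.0% in every setting.

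**Possible repairs.** Replacing only the faulty branch by one averaged test, with the interaction gate kept, leaves 4.9–7.1% overall for five or six points. One averaged test with no gate holds 5%.

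**The case against.** **Primary outcome.** A reader might infer that the trial's confirmatory error rate is 15–21%. The documents do not support that. The primary is one binary comparison at 24 h; one time point has no treatment-by-time interaction, and no section makes pain at other times primary. What stands is that the GEE sentence names the primary outcome, next to a chi-square or Fisher assignment for it, and so attaches the rule where it cannot apply.

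**Benjamini-Hochberg.** The repeated series are secondary, the quoted sentence waives only Bonferroni, and a Benjamini-Hochberg correction is planned for secondary outcomes. If its family contains the time points, the error under no effect is at or below 5%. This stands as a condition on the finding. Defining the family could be left to an analysis plan that is not shown, but section 2.14 states a per-time-point rule without correction, and the two sentences need to be reconciled.

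**Wording.** The primary treatment effect may be a slip for the main effect. That would be the right analysis, but a main effect is one estimate and cannot be assessed at each time point.

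**Power.** A reader might also infer that the plan has no efficient single test when the effect is constant. For pain that is not so: the T1–T5 AUCs in section 2.10.2 are time-weighted summaries that can be compared once between arms.

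**Size.** Any single percentage depends on the assumed correlation, the number of time points, and counting any significant point as an error. Only the range can be defended, though it lies above 5% throughout.

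**Conclusion.** The rule is faulty as written and should be fixed. For each repeated series, the family-wise chance of at least one false positive under no effect is about 9–24% with five or six time points (15–21% for six at correlation 0.7 to 0.3) and about 7–9% with two. These figures assume two-sided tests at 0.05, approximately normal test statistics, exchangeable correlation of 0 to 0.9, and a Benjamini-Hochberg family that does not include the individual time points. They are per series, not across all secondary outcomes. The primary conclusion is unaffected as long as it rests on the one 24 h comparison, so this is a should-fix point, not a threat to the main result.

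**What to change.** In section 2.14:

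1. State that the 24 h comparison is the only primary test and is outside the GEE time-point rule, and remove the primary outcome from the GEE sentence.
2. Replace the two-branch rule with, for example: *For each repeated secondary series, one treatment effect averaged over T1–T5 (for QoR-15, over 24 and 48 h) is tested at 0.05 whatever the result of the interaction test, and its p-value enters the Benjamini-Hochberg family.* The planned T1–T5 AUC can serve as this test for pain; if so, it should enter the family once, not alongside a second averaged test of the same series.
3. Report the 90-day score separately, because an average over all six points would mix it with acute pain at 2–48 h.
4. Show per-time-point differences with 95% CIs as description, or name them explicitly as members of the Benjamini-Hochberg family.

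Dropping the interaction gate matters, since keeping it leaves about 5–7%. The cost is a few sentences, with no new data and no more patients. The downside is that an isolated uncorrected time point can no longer be called significant.
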